## Abstract

**Abstract:**

**Introduction:**

Adolescence is a key period of development for mental health; however, little is known about how (cumulative) daily life experiences impact long-term mental health development in this period, and vice versa. ‘Mental health in the moment’ (MHIM) is an accelerated cohort measurement burst study designed to illuminate these links.

**Methods and analysis:**

The current protocol describes the rationale and design for MHIM, which aims to recruit and follow up approximately 500 adolescents across five age cohorts (in secondary school years S1–S5, aged 11–16 at baseline) and follow them over a 5-year data collection period. Data collection will include online surveys and ecological momentary assessments bursts every 6 months, annual caregiver surveys, the collection of stress biomarker data at three key measurement points and continuous radar-based sleep measurement for a subsample of participants. The study is informed by a young person advisory group input throughout its lifecycle. Data will be analysed using techniques such as dynamic structural equation modelling. The study can provide insights into mental health development from a multitimeframe developmental perspective, including insights into ‘daily life’ intervention targets for improving adolescent mental health.

**Ethics and dissemination:**

The study received ethical approval from the philosophy, psychology and language science ethics committee at the University of Edinburgh (404-2425/3) and the findings will be published in a series of peer-reviewed publications.

STRENGTHS AND LIMITATIONS OF THIS STUDYThe measurement burst design can link day-to-day experiences to long-term development.The accelerated cohort design increases the developmental span but relies on the assumption of cohort invariance.Capturing data during the school day can be challenging because of smartphone use policies.Participant retention over a 5-year period will be challenging.

## Background and rationale

Adolescence is a peak period of vulnerability for the onset and escalation of mental health issues, especially internalising problems.^1 2^ Many important influences on adolescent mental health are those that play out on a day-to-day basis, such as sleep, social interactions and stressors, as well as the cognitive, emotional and behavioural reactions they evoke.^3^,^7^ Importantly, these factors can show reciprocal relations with mental health outcomes.^8^,^10^ However, how cumulative daily life experiences in the formative period of adolescence are linked to long-term mental health development is little understood. The current protocol describes a planned multitimeframe longitudinal study that can help illuminate these links. In doing so, it seeks to offer new insights into intervention targets that lie within the daily life experiences of adolescents.

There is no universally accepted definition of adolescence; however, there is a strong consensus that it represents a critical period for mental health development.^2 11^ The period is characterised by a range of biological (eg, hormonal), social and psychological changes with implications for mental health. For example, adolescents must navigate challenges such as identity formation,^12^ an intensification of the importance of peer relationships,^13^ the emergence of romantic involvement,^3^ circadian rhythm shifts^14 15^; and heightened emotional and behavioural regulation challenges.^16^,^18^ These occur in the context of increased expectations of independence and diminishing parental monitoring.^19^ Further, increased plasticity of the brain and systems such as the hypothalamic–pituitary–adrenal axis creates pathways by which experiences during this time can have long-term significance for mental health trajectories.^6^

These considerations make a developmental perspective essential for understanding adolescent mental health,^2 12^ and correspondingly, important advances in our understanding of mental health in this period have come from longitudinal study designs.^20^,^22^ However, the presence of longer-term changes occurring over months and years with connections to experiences occurring over minutes, hours and days^23^,^28^ necessitates studies capturing data over multiple timescales.^29^ Few studies have attempted to link ‘developmental’ (months, years) and ‘momentary’ (minutes, hours, days) time in this way, tending to focus on one or the other timeframe.^30^

Measurement burst designs^31^ can help bridge this gap and illuminate the links between daily life experiences and long-term mental health development. Measurement burst designs involve repeated ‘bursts’ of ecological momentary assessment (EMA) data collections. In each EMA burst, short surveys can be used to gather intensive in-the-moment data about experiences as they play out in the course of participants’ daily lives.^32^ This is commonly implemented via smartphone-based surveys administered several times a day over the course of a number of days or weeks.^33 34^ EMA has offered numerous insights into the mental health of young people,^35^ such as how specific affective dynamics (eg, emotional lability and inertia) are related to different mental health outcomes.^36^ Repeating the EMA at regular intervals in a burst design facilitates the examination of developmental change and/or the reciprocal relations between daily life experiences and longer-term change.^37^ However, very few EMA measurement burst studies have been conducted to date and only a handful focus on mental health,^38 39^ with studies in adolescence particularly lacking.^40^

### The present study

Given the need for evidence on the reciprocal relations between daily life experiences and long-term mental health development in the critical period of adolescence, we here outline our plans for a multitimeframe study that combines traditional caregiver and young person surveys, EMA bursts, passive sleep sensing and biosampling. The study will use an accelerated cohort design^41^ to capture developmental data spanning ages 11–20 over a 5-year data collection period. A multi-informant approach including both caregiver and adolescent self-reports will be taken in line with the fact that young people may show different behaviours in different contexts and with different informants.^42 43^ Caregivers and adolescents will complete online surveys and adolescents will additionally complete smartphone-based EMA surveys and provide biosamples. A subsample will also complete a radar-based ambient sleep measurement protocol. Overarching research questions will include:

How do cumulative daily life experiences such as social experiences and daily stressors impact on mental health development across adolescence?How do changes in mental health status (eg, increases or decreases in depression) impact on daily life experiences (eg, emotions and their regulation)?How do changes in factors such as emotion regulation in daily life and sleep over the course of adolescence impact on mental health?What are the developmental differences across adolescence in the daily life influences on, and manifestation of, mental health issues?

## Methods

### Patient and public involvement

The mental health in the moment young person advisory groups (MHIM-YPAG), alongside other YPAGs, were consulted on the design of the study and will provide input throughout the lifecycle of the project, including the design of the study, interpretation of results and dissemination of findings. Thus far, YPAGs have provided advice on which mental health influences and outcomes to include in the study, the engagement strategies^44^ and the codesign procedure.^45^ Full details of the planned coproduction are provided in a dedicated publication^45^; however, in brief, the process will involve adolescents aged 11–18 engaged via a series of YPAGs across >35 sessions over the project. These are divided into a ‘predata collection’ phase and a ‘data collection phase’. Sessions will focus on topics such as ‘mental health concepts’, ‘recruitment strategy and materials’, ‘mental health instruments and survey design feedback’, ‘hair sampling and EMA and sleep measurement’, ‘data chat and dissemination’, ‘training needs’, ‘training’, ‘informal team building’ and ‘output’. Given the emphasis on young people’s input, the design described in this protocol is subject to change based on the views of the MHIM-YPAG.

### Overview

The study will use a measurement burst accelerated cohort design.^31 46^ Specifically, every 6 months over a 5-year period, adolescents will complete an EMA burst and an online survey. At baseline (anticipated beginning in November 2025), five cohorts of approximately n=150 will be recruited from schools in the UK (see figure 1) to facilitate developmental data spanning ages 11–20 in 5 years of data collection (ending in December 2030). We aim to keep the intervals between data collections similar across young people but will test and, if necessary, later statistically adjust for any effects of individual differences in intermeasurement time intervals at the analysis stage.

**Figure 1 F1:**
[figure not shown]
(A) The accelerated cohort design with 5 age cohorts followed over a 5-year period. The cohorts will be recruited by school year (S1–S5), which corresponds approximately to age 11/12 to 15/16. (B) The data collection schedule for mental health in the moment.

Hair samples will be collected at the end of selected EMA/online survey bursts to provide biomarkers of stress concurrent with EMA periods.^47 48^ Participants who are unable or who prefer not to provide a hair sample will be offered the option to provide a nail sample. This will be used to impute hair cortisol and cortisone values for these participants. A pilot study, which will analyse the correlation between hair and nail sample biomarker values, will be used to validate this method.

Participants will be offered compensation for taking part, scaled to their level of engagement across the different components (surveys, EMA, biosampling and sleep measurement).

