The *ambient sleep measures* will be collected using radar-based technology, which will run continuously for a period that includes the EMA/survey bursts. These data will be collected for a subsample of approximately n=50 of the youngest cohort, to capture a critical period of development for sleep. While polysomnography (PSG) is the gold standard for sleep measurement, it is obtrusive and costly and therefore impractical for measurement burst studies. Recent advances in radar-based technologies allow sleep to be measured with a high degree of accuracy (as validated against PSG) in the course of people’s daily lives.^57^ Data will be used to derive indices of sleep volume and timing. This will be complemented by subjective sleep measures collected as part of the EMA daily diary.

*Hair samples* will be collected at three time-points throughout the study. These will be used to obtain biomarkers of accumulated biological stress over the period concurrent with the EMA period and over the last 6 months.^47 48^ These will be analysed to quantify cortisol and cortisone levels. We are currently piloting the use of nail samples to help us impute hair cortisol/cortisone levels for those unable or unwilling to provide a hair sample. To ensure that possible confounding factors are measured, participants will also complete a set of questions in the *biosampling survey* factors such as medications and hair treatments (eg, dye, bleach, relaxers or hair straighteners) that have been shown in previous work to impact hair cortisol readings.^58 59^

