### Statistical analysis

Data will be analysed using a range of approaches depending on the specific research question. A majority of research questions will be addressed using DSEM that can account for the multilevel, time-series (in the EMA) and longitudinal nature of the data.^65^ This can be extended to a measurement burst design to, for example, analyse the cross-lagged relations between day-to-day dynamics and long-term development.^66^ Longitudinal analyses will depend on the assumptions of cohort and longitudinal measurement invariance,^67^ which will be tested prior to the main analyses. Missing data will primarily be dealt with using full information maximum likelihood estimation (FIML), Bayesian estimation, attrition weighting or multiple imputation, depending on the analysis, all of which provide unbiased estimates under an assumption of missing at random.^68^ Robust estimators, such as robust maximum likelihood estimation, will be used to deal with violations of maximum likelihood estimator assumptions.

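### A pilot hair–nail correlation does not by itself establish that hair cortisol and cortisone can be imputed from nail; calibration and prediction error should be the criterion

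*Protocol article*

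**What the plan says.** The plan for nail samples is in two places in the protocol article.

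- **Methods, Overview (text after Figure 1).** "Participants who are unable or who prefer not to provide a hair sample will be offered the option to provide a nail sample". The purpose follows: "This will be used to impute hair cortisol and cortisone values for these participants". So does the check: "A pilot study, which will analyse the correlation between hair and nail sample biomarker values, will be used to validate this method".
- **Measures overview, hair samples.** The work is still in progress: "We are currently piloting the use of nail samples to help us impute hair cortisol/cortisone levels". Hair samples "will be collected at three time-points throughout the study" and are meant to give "biomarkers of accumulated biological stress over the period concurrent with the EMA period and over the last 6 months". No time window is given for nail. Medication and hair treatments are recorded in the biosampling survey as possible confounders of hair readings.

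The Statistical analysis section lists general missing-data methods: full information maximum likelihood, Bayesian estimation, and "attrition weighting or multiple imputation, depending on the analysis, all of which provide unbiased estimates under an assumption of missing at random". It does not tie any of them to the nail step. The article gives no hair–nail correlation, no expected share of nail-only participants and no number of hair–nail pairs.

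**The concern.** The article fixes a use (predicting one biomarker from another) and a validation criterion (their correlation), and the two do not match. Imputation needs the hair value to be predicted on the right scale, with a known and tolerable error, in the people for whom it is missing. A correlation is unchanged by any shift or positive rescaling of either measure, and it sets no limit on prediction error.

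The pilot carries unusual weight here. Nail is offered to those who do not give hair, so the main study as described yields no participants with both samples. The hair–nail relation must come from the pilot and be carried over to a group defined by being unable or unwilling to give hair. If the pilot reports only a correlation, nothing checks that transfer.

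At stake are the analyses that use the biomarker as the measure of stress. The Discussion names effects of cumulative daily experiences on stress among the questions the data can address, and when the biomarker measures stress, cortisol is the outcome.

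**Working it through.** The plan states no figure on this point, so there is nothing to reproduce. The check uses closed forms and simulation.

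**Inputs.** Assumed, because the article does not give them: hair–nail correlation r = 0.3, 0.5 or 0.7; nail-only share s = 10% or 30%; a true standardised slope of 0.3; 68 calibration pairs. The figure 68 is the size of the main pilot in the Piloting section, which is not stated to be the hair–nail pilot. The analysed sample is 500, from 5 cohorts × the minimum of 100 in the Sample size section.

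**1. Correlation against calibration.** Let hair have mean 5 and SD 1, and let nail = 0.4 × hair + 1 + noise with SD 0.3. Then r = 0.4 / √(0.16 + 0.09) = 0.4 / 0.5 = 0.80. Mean nail is 0.4 × 5 + 1 = 3, so using nail directly for hair is off by 2 hair SDs on average. The high correlation does not reveal this.

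**2. Prediction error after perfect calibration.** Explained share is r²; residual SD is √(1 − r²) hair SDs.

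- r = 0.3: 9% explained, residual SD 0.95
- r = 0.5: 25% explained, residual SD 0.87
- r = 0.7: 49% explained, residual SD 0.71

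**3. Precision of the pilot r.** With 68 pairs and r = 0.5, the Fisher z interval is tanh(0.549 ± 1.96/√65), or 0.30 to 0.66.

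**4. Cortisol as outcome, single regression imputation from nail alone.** With standardised measures the imputed value is r × nail. If nail relates to the covariate only through hair, its covariance with the covariate is r times that of hair, so the slope among nail-givers is r² times the true slope. Pooled ratio = (1 − s) + s·r² = 1 − s(1 − r²).

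| r | s | Formula | Simulated ratio | Coverage of nominal 95% interval |
|---|---|---|---|---|
| 0.3 | 10% | 0.909 | 0.912 | 0.90 |
| 0.5 | 10% | 0.925 | 0.923 | 0.91 |
| 0.7 | 10% | 0.949 | not run with pilot calibration | not run |
| 0.3 | 30% | 0.727 | 0.724 | 0.40 |
| 0.5 | 30% | 0.775 | 0.787 | 0.60 |
| 0.7 | 30% | 0.847 | 0.847 | 0.79 |

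The model standard error was 0.95 to 1.00 of the empirical standard error, so coverage is lost mainly through bias in the slope.

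**5. Another measurement model.** If hair and nail are equally good indicators of a common cortisol level, both have the same covariance with the covariate, and the ratio becomes 1 − s(1 − r). At s = 30% this is 0.79, 0.85 and 0.91 for r = 0.3, 0.5 and 0.7, which is less shrinkage than in step 4.

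**6. Cortisol as predictor, calibrated regression imputation.** Under the model of step 4, the covariance with the outcome and the variance of the predictor both shrink by 1 − s(1 − r²), so the slope is preserved. Simulated ratios were 0.99 to 1.00, with coverage 0.94 to 0.95. Under the model of step 5 the ratio is [1 − s(1 − r)] / [1 − s(1 − r²)]. At s = 30%, r = 0.5 this is 0.85 / 0.775 = 1.10, which is inflation, not dilution.

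**7. Multiple imputation.** Using nail plus the analysis variable, with 20 imputations and Rubin's rules, slope ratios were 0.99 to 1.02 and coverage 0.94 to 0.955, with cortisol as predictor or as outcome.

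**The case against.** The strongest reply is that the article describes an ongoing pilot in one sentence. Reporting a correlation does not mean that no calibration will be done. The imputation model, its covariates and the handling of its uncertainty are details that a journal article commonly leaves to a fuller plan. The article says nail samples help with imputation, which allows for other inputs. Multiple imputation and Bayesian estimation are already among the study's methods, and step 7 shows that proper multiple imputation removes the problem. Biosamples are taken at only three time-points, and none of the four overarching research questions names cortisol.

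Much of this stands. The unstated imputation model is not an error in itself, and the size of any effect rests on assumed r and s. What does not fall away is the criterion, because the article states it: the correlation is what is to validate the method. A correlation is a sensible first check and fixes the explained variance, but it is not sufficient.

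A reader might go further and infer that every biomarker association will be diluted and that intervals will be too narrow. The documents do not support this. Nothing in the article says imputed values will be entered as if measured. Step 6 shows no dilution with cortisol as predictor. In step 4 the standard errors were close to the true sampling variation, so the under-coverage there is mainly a result of bias.

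**Conclusion.** The point holds for the validation criterion. A hair–nail correlation alone does not establish that hair cortisol and cortisone can be imputed from nail.

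The consequence is conditional. It arises when cortisol is the outcome and hair is singly imputed from nail alone. Slopes then fall by about 5% to 9% at a nail-only share of 10%, and by 15% to 27% at 30%, for assumed r between 0.3 and 0.7. The loss is smaller if hair and nail are parallel indicators of one cortisol level. The article supplies neither r nor the nail-only share, so these are illustrations over a range and not forecasts.

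Importance is moderate: biosampling is a named component of the study, but a limited one. The pilot is described as under way, so the criterion may still be open to change.

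**What to change.** 1. **Criterion.** Using the same pilot pairs, replace the correlation with limits set in advance on cross-validated prediction error and on calibration intercept and slope, separately for cortisol and cortisone. The correlation can still be reported.
2. **Imputation.** Bring nail data in through multiple imputation, or a latent-cortisol measurement model, that includes the analysis-model variables and the recorded medication and hair-treatment confounders. Carry the uncertainty of the pilot calibration into the standard errors. State the assumption being made: pilot participants, hair-givers and nail-givers share the same hair–nail relation given the recorded variables.
3. **Sensitivity.** Report a hair-only analysis alongside. Making it the primary analysis would be debatable, because it drops a self-selected group.
4. **If calibration fails.** Do not impute hair from nail.

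The cost is a little more analysis work and somewhat wider intervals. No new samples are needed.

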### Participants

Our baseline sample will be 750 adolescents from schools in Scotland (oversampling at baseline to help ensure adequate numbers remain at follow-up waves to support longitudinal analyses). Though definitions of adolescence vary, there is general consensus that ages 11–19 fall within adolescence within Western contexts^49^ and this age range will thus be the focus of the present study. The recruitment and data collection will be implemented via local schools, reflecting the fact that the school environment is of considerable importance with respect to fostering the development of good mental health and potentially for the delivery of preventive interventions.^50^ Sex and gender differences have been shown to be important in mental health^51 52^; therefore, we will aim to ensure sex and gender diversity in the sample.

At baseline, n=150 participants from each of 5 groups defined by school year will be recruited: secondary school years 1, 2, 3, 4 and 5 at the time of recruitment (approximately corresponding to an age range of 11–16). If necessary, refreshment samples will be considered to counteract dropout.^53 54^ Participants will be approached via their schools, with the research team sharing information about the study via posters and presentations and links for signing up shared by schools with parents/caregivers.

To help maximise sample diversity and minimise recruitment bias, our goal is to work with schools situated in both rural and urban areas with varying levels of socioeconomic deprivation. We will take measures to help ensure that our recruitment materials and strategies are inclusive, such as producing poster adverts depicting young people of different genders and ethnicities and seeking advice on our strategy and materials from our YPAG.

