#### Sample size

The sample size was determined based on previous Monte Carlo simulations of DSEMs, which will represent our primary analysis approach. These have suggested that 50 respondents with at least 10 measurement points are needed to avoid small sample bias for random effects, as well as to provide adequate coverage for within-person and between-person effect sizes of a magnitude that are likely to be of clinical importance.^71 72^ We also conducted our own Monte Carlo simulations that used realistic parameters from previous EMA models, which confirmed that a sample size of 50 should be adequate. However, given the likelihood of attrition over time and of missingness within each burst, we will aim for a minimum of 100 respondents per cohort (with the goal of over-recruiting by up to 50% at baseline to allow for attrition) to help ensure an adequate sample size for within-cohort analyses. Specific Monte Carlo analyses may be conducted to assess the extent to which our realised sample size can support particular analyses.

To help maximise retention, we have codesigned several strategies with a YPAG and will continue to refine these strategies with our current MHIM-YPAG.^73^ These strategies were based on a narrative review^74^ and can be organised into four domains: (1) using a codesign approach to ensure the study is appealing for adolescents (eg, consult the YPAG on the study contents to ensure it addresses questions that are relevant for them,^75^ (2) rapport/relationship building with schools and participants (eg, select and train staff for ability to build rapport with participating schools/adolescents; visit schools to present the project and recruit students within each school to act as ‘project ambassadors’), (3) offering reimbursement and incentives (eg, offering shopping vouchers to participants, embedding ‘mental health facts’ in the data collection process, offering school-level feedback) and (4) minimising barriers and burden (eg, using tried and tested technology to minimise glitches, avoiding exam times, not requiring caregiver participation as an inclusion criterion for adolescent participation).

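### Recruiting by current school year makes the S5 cohort conditional on still being enrolled, so S5 and the younger cohorts may come from different populations at the same age

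*Protocol article*

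**What the plan says.** On who enters, the Participants section states that "n=150 participants from each of 5 groups defined by school year will be recruited: secondary school years 1, 2, 3, 4 and 5", with the year taken at the time of recruitment. On the route in, it says "Participants will be approached via their schools" and "The recruitment and data collection will be implemented via local schools". No route is described for young people who are not enrolled. The legend to Figure 1 puts S1 to S5 at roughly 11/12 to 15/16, and the Overview section plans six-monthly bursts for five years to span ages 11–20. No rule removes a participant who leaves school.

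On the assumption that joins the cohorts, the box of strengths and limitations after the abstract says: "The accelerated cohort design increases the developmental span but relies on the assumption of cohort invariance". The Statistical analysis section says: "Longitudinal analyses will depend on the assumptions of cohort and longitudinal measurement invariance". It adds that this will be tested before the main analyses, and gives no criterion or detectable difference.

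On same-age comparisons, the Limitations section plans to study measurement reactivity by comparing, at each age, participants who have been in the study for different lengths of time.

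**The concern.** An accelerated design treats the S5 cohort from about 15.5 onwards as interchangeable with S4, S3, S2 and S1 participants once they reach the same age. The entry rule differs, however. A young person who left school before S5 was sampled cannot be in S5, but a similar person recruited in S1–S4 can be in the study and stay in it after leaving.

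Two uses of the data are exposed:

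- **Joining trajectories.** Part of any difference between S5 and the younger cohorts at a shared age could be selection on staying at school rather than age, birth cohort or chance.
- **Reactivity.** Around age 16 the newest entrants are S5, so the group with the least time in study is also the enrolled-only group.

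None of the stated safeguards is aimed at this. The missing-data methods and attrition weights deal with people who were recruited and then lost. The optional weights in the Complex survey design section use census demographics and do not name school leaving. Seeking schools across rural, urban and more or less deprived areas acts between schools, not on who has left a given school.

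**Working it through.** **1. The plan's own numbers.** The Sample size section says "we will aim for a minimum of 100 respondents per cohort". It then allows baseline recruitment to exceed that figure by as much as half. This gives 100 × 1.5 = 150 per cohort and 5 × 150 = 750, which matches the Participants section. The basis of the 100 is small-sample bias and coverage in dynamic structural equation models, for analyses within cohorts. It was not set for a comparison between cohorts.

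**2. Where S5 overlaps the others.** Taking mid-year baseline ages from the Figure 1 legend and adding five years gives approximately:

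| Cohort | Age covered | Overlap with S5 |
|---|---|---|
| S1 | 11.5–16.5 | 15.5–16.5 |
| S2 | 12.5–17.5 | 15.5–17.5 |
| S3 | 13.5–18.5 | 15.5–18.5 |
| S4 | 14.5–19.5 | 15.5–19.5 |
| S5 | 15.5–20.5 | – |

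Only about 19.5–20.5 is covered by S5 alone. No cohort comparison is possible there.

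**3. Size of the shift.** Let p be the share who leave before S5 is sampled and d the standardised difference between leavers and stayers. A cohort of stayers differs from the full population by p × d. Neither value is in the article. Assumed: p = 10–20%, d = 0.3–0.5 SD.

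- Low end: 0.10 × 0.3 = 0.03 SD
- High end: 0.20 × 0.5 = 0.10 SD

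**4. Would a comparison of cohort means show it?** For two independent means on one occasion, SE = √(1/n₁ + 1/n₂). This gives √(2/150) = 0.115 SD for 150 v 150, √(2/100) = 0.141 SD for 100 v 100, and √(1/150 + 1/600) = 0.091 SD for S5 against all younger cohorts together. Two-sided 5% power (the level is assumed; the article gives none):

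| Shift | 150 v 150 | 100 v 100 | 150 v 600 |
|---|---|---|---|
| 0.03 SD | 5.8% | 5.5% | 6.2% |
| 0.10 SD | 13.9% | 10.9% | 19.5% |

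The difference detectable with 80% power is (1.96 + 0.84) × SE: 0.32 SD, 0.40 SD and 0.26 SD respectively. School clustering would raise these; with an assumed design effect of 1.5, 150 v 150 becomes 0.40 SD. Repeated bursts could add some precision.

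**5. What would make it visible.** For the shift to reach 0.256 SD (the 150 v 600 threshold before rounding), leavers would have to differ by 0.256/0.10 = 2.6 SD at p = 10%, or 0.256/0.20 = 1.3 SD at p = 20%.

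**6. Which test the article plans.** A measurement-invariance test asks whether item parameters are equal across groups. A change in who is in the group can move the mean or the trajectory while those parameters stay equal. Passing such a test would therefore not settle this point, and the power figures in step 4 describe a different test.

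**The case against.** The strongest reply is that the article gives no school-leaving age, no leaver share and no difference between leavers and stayers. S5 entrants are only about 15/16, and anyone who leaves during S5 after recruitment is already in the cohort. Only those gone before sampling matter, and they may be few. This stands: the difference in entry rule is in the document, but its consequence is assumed.

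Second, low power here largely reflects a small effect. The whole assumed range lies below the 0.115 SD standard error of a two-cohort difference. This also stands, and it limits the harm to pooled trajectories.

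Third, many of the research questions concern dynamics within a person or within a cohort, where a modest shift in level between cohorts need not bias the estimate. That is fair, but it does not protect analyses across cohorts or the reactivity comparison.

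Fourth, reliance on cohort invariance is disclosed, and representativeness will be examined. This is true in general terms, but neither statement addresses conditioning one cohort on enrolment. The daily attendance item might allow leaving to be partly recovered, though it is not described as recording it.

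Finally, if younger participants drop out when they leave school, the contrast shrinks and becomes an attrition problem. That is possible, and recording leaving status would help to show it.

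**Conclusion.** The point holds in a limited form. Entry to S5 is conditional on enrolment at about 15/16, later leavers in S1–S4 are not excluded, and nothing in the article targets the difference. Under the assumed inputs the shift is 0.03–0.10 SD: small, and unlikely to be noticed in a comparison of cohort means.

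A reader might infer three stronger things that the article does not support:

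- **That a cohort difference is shown to be built in.** Only the eligibility rule is; whether it produces a difference depends on figures that are not given.
- **That the planned invariance test is shown to be too weak.** The article states no criterion for it, and the power figures belong to a simple comparison of means.
- **That the upper end of the age range rests mainly on S5.** S4 reaches about 19.5 and S3 about 18.5, so only about the final year rests on S5 alone. That year is at or beyond the edge of the 11–19 focus given in the Participants section.

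**What to change.** Make three changes, none of which needs extra recruitment:

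- **Record leaving.** Add school-leaving status and date to the six-monthly young person survey for all cohorts. The article says that measures may still change, so there is room for an item.
- **Match the entry condition.** Wherever S5 is compared or joined with S1–S4 at overlapping ages, and in the reactivity comparison, add an analysis restricted to S1–S4 participants who were still at school when they reached the stage at which S5 was sampled. Report it beside the unrestricted analysis.
- **Narrow the claim.** Describe results for the ages covered by S5 alone as applying to young people who stayed on to S5.

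Reweighting S5 entrants is not a substitute, because weights on stayers cannot bring back leavers who were never eligible.

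The cost is one short item, a smaller and less precise overlap comparison, and a narrower statement at the oldest ages. The restricted analysis does not gain power; it removes the difference in eligibility from the comparison. For the S1 cohort the necessary status is known only late in follow-up, so the item should be in place from the start.
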